**Abstract**

**Introduction**: Electrodiagnostic (EDX) testing is fundamental for diagnosing neuromuscular disorders. However, interpretation is time-consuming and requires specialized expertise. This trial aims to evaluate whether an AI-assisted approach can improve the accuracy and quality of EDX reports compared with conventional physician-only interpretation.

**Methods and Analysis**: This single-center randomized controlled trial will enroll 200 adult patients scheduled for routine EDX testing at Rambam Health Care Campus, Haifa, Israel between January 21, 2025, and February 21, 2025. Participants will be randomized 1:1 to either AI-assisted physician reporting or standard physician-only reporting. The AI intervention (INSPIRE) is a multi-agent framework built upon ChatGPT-4o large language models hosted on the AZURE AI platform, which will generate preliminary EDX reports for physician review and editing. The primary outcome is report quality, assessed using the AI-Generated EMG Report Score (AIGERS; range 0-1). Secondary outcomes include measures of AI-physician collaboration efficiency and physician satisfaction with the tool. A two-week calibration phase will precede trial initiation to optimize AI integration.

**Ethics and Dissemination**: This study was approved by the Rambam Healthcare Campus Institutional Review Board. Results will be published in peer-reviewed journals and presented at scientific conferences.

**Trial Registration**: ClinicalTrials.gov Identifier: [NCT06902675](https://clinicaltrials.gov/study/NCT06902675)

**Key Points**

- This trial evaluates the impact of AI-assisted interpretation on the quality of electrodiagnostic (EDX) reports compared to standard physician-only interpretation.
- The AI system (INSPIRE) is a multi-agent framework using LLMs to generate preliminary EDX reports that are then reviewed and edited by physicians.
- Outcomes include report quality (measured by the AIGERS score), efficiency metrics, and physician satisfaction with the AI tool.

**1. Administrative Information**

**1.1 Title**

Assessment of AI‑Assisted Neuromuscular EDX Reporting on Diagnostic Quality: A Randomized Controlled Trial Using a Multi-Agent LLM Framework (INSPIRE)

**1.2 Trial Registration**

ClinicalTrials.gov Identifier: [NCT06902675](https://clinicaltrials.gov/study/NCT06902675)
MyTrial.gov registration: [MOH_2025-01-22_013868](https://my.health.gov.il/CliniTrials/Pages/MOH_2025-01-22_013868.aspx).

**1.3 Protocol Version**

Version 1.0, January 2, 2025

**1.4 Funding**

No external funding was received for this study.

**1.5.2 Trial Sponsor**

Not funded

**2. Introduction**

**2.1 Background and Rationale**

**2.1.1 Intended Use of the AI Intervention**

The INSPIRE AI framework is intended to assist neurologists in interpreting electrodiagnostic (EDX) tests (including electromyography and nerve conduction studies) and generating diagnostic reports. The primary purpose is to reduce documentation burden, standardize reporting, and potentially improve diagnostic accuracy. The intended users are board-certified neurologists who regularly perform EDX tests in clinical practice.

Within the clinical pathway, EDX studies are conducted to evaluate patients with suspected neuromuscular disorders. Currently, physicians manually interpret the raw data and compose reports, a process that is time-consuming and subject to variation in quality and completeness. The INSPIRE system will generate a preliminary report based on the raw EDX data, which will then be reviewed, verified, and edited by a neurologist before finalization. This is expected to streamline workflow while maintaining or improving diagnostic accuracy.

**2.1.2 Pre-existing Evidence for the AI Intervention**

The INSPIRE framework builds upon recent advances in large language models (LLMs) that have shown promise in clinical documentation and decision support. Prior to this trial, we conducted a retrospective study using old version of INSPIRE using retrospective EDX reports. This phase demonstrated the technical feasibility of the system to interpret EDX data and generate structured reports.

There is currently limited published evidence specifically evaluating AI for EDX interpretation. However, studies in other medical specialties have shown that AI can assist with clinical documentation and reduce physician workload. Our approach is novel in applying a multi-agent LLM architecture to this specific clinical task.

**2.2 Explanation for Choice of Comparators**

The control arm (physician-only reporting) represents the current standard of care for EDX interpretation. This comparator was chosen to directly assess whether the addition of AI assistance provides measurable improvements over existing clinical practice. By comparing AI-assisted reporting to standard physician reporting, we can determine the added value of the AI intervention in real-world clinical settings.

**2.3 Objectives**

Primary objective: To determine whether AI-assisted EDX interpretation improves the quality of diagnostic reports compared to standard physician-only interpretation.

Secondary objectives:

1. To assess the technical performance of the AI system (sensitivity, specificity) for detecting abnormal EDX findings
2. To evaluate physician satisfaction with the AI system
3. To assess the impact of AI assistance on documentation time and workflow
4. To identify specific areas where AI assistance is most beneficial in EDX reporting

**2.4 Trial Design**

This is a single-center, randomized controlled trial with two parallel arms and 1:1 allocation ratio:

1. Intervention arm: AI-assisted physician EDX report generation
2. Control arm: Standard physician-only EDX report generation

**3. Methods: Participants, Interventions, and Outcomes**

**3.1 Study Setting**

The trial will be conducted at the neuromuscular outpatient clinic of Rambam Health Care Campus, a tertiary care academic medical center. All participants will undergo EDX testing according to standard clinical protocols.

**3.1.1 Integration Requirements**

The implementation of the INSPIRE system requires the following:

Onsite requirements:

- Secure, HIPAA-compliant workstations with access to the AZURE AI platform
- Integration with the electronic health record (EHR) system for accessing patient history
- Dedicated secure server for data processing

Offsite requirements:

- Secure Azure cloud infrastructure for hosting the AI models
- Encrypted data transmission channels compliant with hospital IT security protocols
- Regular system maintenance and updates by the technical team

**3.2 Eligibility Criteria**

**3.2.1 Participant-Level Inclusion Criteria**

1. Age ≥18 years
2. Referred for routine EDX testing at the neuromuscular clinic
3. Able to provide informed consent
4. Scheduled for complete EDX evaluation including both nerve conduction studies and needle EMG

**3.2.2 Participant-Level Exclusion Criteria**

1. Age <18 years
2. Patients undergoing single-fiber EMG testing
3. Incomplete EDX testing (lacking either nerve conduction studies or needle EMG)
4. Inpatient status
5. Previous EDX testing within the past three months

**3.2.3 Input Data-Level Inclusion Criteria**

1. Complete nerve conduction study data including sensory and motor studies
2. Complete needle EMG examination of at least three muscles
3. High-quality recordings with minimal artifacts
4. All standard measurements recorded (amplitude, latency, conduction velocity)
5. Patient demographic data and clinical history available

**3.2.4 Input Data-Level Exclusion Criteria**

1. Incomplete measurement sets (missing amplitude, latency, or velocity data)
2. Technical failures during recording
3. Corrupted or inaccessible digital files
4. Non-standard recording protocols

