**3.3.3 Handling Poor-Quality Input Data**

If the EDX data contains artifacts or is of insufficient quality, the following procedure will be implemented:

1. If specific measurements are missing but the overall study is interpretable, the report will be discarded base upon the examiner decision
2. If the data quality falls below a predetermined threshold (>30% of measurements affected by artifacts or >2 critical measurements missing), the case will be excluded from AI analysis and documented as a technical failure

For both arms, poor-quality data will be documented.

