**4.1.2 Concealment Mechanism**

Allocation will be concealed using sequentially numbered, opaque, sealed envelopes that will be opened only after the participant has been enrolled and immediately before the EDX study begins.

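### Protocol sections 3.2.3/3.2.4 and 3.3.3 give different decisions on a randomized study with one or two missing values, and neither separates an absent response from a value not obtained

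*Protocol*

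**What the plan says.** Three sections of the Protocol govern incomplete recordings.

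- **3.2.3, input-level inclusion.** Item 4 requires "All standard measurements recorded (amplitude, latency, conduction velocity" among its conditions. Item 3 requires "High-quality recordings with minimal artifacts".
- **3.2.4, input-level exclusion.** Item 1 excludes "Incomplete measurement sets (missing amplitude, latency, or velocity data", with no permitted number or share. Items 2 to 4 deal separately with technical failures, unusable files and non-standard protocols.
- **3.3.3, poor-quality input.** Item 1 reads: "If specific measurements are missing but the overall study is interpretable, the report will be discarded base upon the examiner decision". Item 2 sets a threshold, ">30% of measurements affected by artifacts or >2 critical measurements missing", above which "the case will be excluded from AI analysis and documented as a technical failure". For both arms, the section asks only that poor-quality data be documented.

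On timing, section 4.1.2 has the envelope opened "immediately before the EDX study begins". The Protocol does not define a missing value, an incomplete set or a critical measurement, and it does not mention absent or unobtainable responses.

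**The concern.** Two separate weaknesses meet here.

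First, the same recording can meet two rules with different outcomes. Staff working from 3.2.4 would exclude it; staff working from 3.3.3 would refer it to the examiner. Because the recording is made after allocation, the choice decides which randomized patients contribute an AIGERS score. Section 4.2 states that the neurologists writing the reports know the arm, and section 4.1.3 has the treating neurologists act on the envelope. Nothing shields the examiner's decision from knowledge of allocation.

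Second, a nerve without an obtainable response yields no latency and no velocity to enter, and that absence is itself an abnormal finding. If such blanks are counted as missing, exclusion depends on the disease and not on the quality of the recording. That would bear on the sensitivity outcome (3.4.2 item 4), on the polyneuropathy and mononeuropathy subgroups and the normal/abnormal stratification (5.2.6), and on the secondary objective "To identify specific areas where AI assistance is most beneficial in EDX reporting".

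**Working it through.** No figure in the Protocol is at stake, so the check sets the rules side by side.

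**Step 1. Apply each rule to the same study.**

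| Recording | 3.2.3 / 3.2.4 | 3.3.3 |
|---|---|---|
| One amplitude, latency or velocity value missing, study interpretable | Excluded | Examiner decides; below the mandatory threshold |
| Two such values missing, study interpretable | Excluded | Examiner decides; below the mandatory threshold |
| Three or more such values missing, all critical | Excluded | Excluded from AI analysis, logged as technical failure |
| Artifacts more than minimal but in no more than 30% of measurements | Fails 3.2.3 item 3 | Below the mandatory threshold |

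The first, second and fourth rows conflict. The third agrees on exclusion.

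**Step 2. Can timing reconcile them?** It could if 3.2.3/3.2.4 screened patients before randomization and 3.3.3 acted afterwards. It does not: the envelope is opened before the EDX study starts (4.1.2), so both rules can act only on data recorded after allocation.

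**Step 3. Is application the same in both arms?** The coordinator's completeness check appears in 3.3.4 only as part of transferring data to the AI. Item 2 of 3.3.3 excludes from AI analysis, a phrase with no evident meaning for a physician-only report. The one instruction given for both arms is to document. The text therefore does not guarantee identical exclusion by arm.

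**Step 4. What happens to an absent response?** Suppose unobtainable values count as missing and as critical; the Protocol says neither. One nerve without a response leaves latency and velocity blank, so 2 values. That already meets the exclusion in 3.2.4 but does not exceed the limit in 3.3.3. Two such nerves leave 2 × 2 = 4 values, and 4 > 2, so 3.3.3 would also exclude the study and record it as a technical failure. Choosing one threshold is therefore not enough; *missing* must be defined as well.

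**Step 5. Link to the analysis.** Section 5.2.5 uses complete cases if less than 5% is missing and multiple imputation above 5%. With 200 participants, 0.05 × 200 = 10. If input exclusions count as missing outcome data, which 5.2.5 does not settle, more than 10 of them would change the primary analysis method. The choice between the two input rules could then also decide which method is used.

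**The case against.** The strongest reply is that 3.2.4 is about acquisition. The items beside item 1 concern technical failures, files and recording protocols, so *missing* most naturally means not acquired or lost, and a no-response entry may already count as recorded. Coding of unobtainable responses may also sit in a data manual or SAP that is not shown. Restricting the AI to complete input is a legitimate design choice, and no bias in the randomized AIGERS comparison has been demonstrated.

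Much of this stands. A reader might infer that 3.2.4 removes severe neuropathies from the trial. The documents do not support that: no section says an absent response counts as missing, and no frequency is given. The wording permits that reading but does not require it.

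Two further inferences also go too far. One is that 3.3.3 keeps studies with up to two missing values. Item 1 provides for a discretionary discard, not a right to retain; the tolerance is only implied by that discretion and the threshold. The other is that the 3.3.3 threshold can never be reached. Its artifact limb does not depend on 3.2.4 item 1, and critical measurements are undefined and could include needle EMG data, which are also AI input (3.3.2).

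What the reply does not remove is the conflict itself. Eligibility and input handling are fixed in the Protocol, and they are fixed in two ways.

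**Conclusion.** The point holds as an inconsistency with an undefined term. A randomized study with one or two missing amplitude, latency or velocity values is excluded under 3.2.3/3.2.4 and left to the examiner, below the mandatory threshold, under 3.3.3. This follows from the text alone and rests on no assumption.

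The absent-response part is conditional. If blanks from unobtainable responses are treated as missing, exclusion would select by disease severity, and sensitivity and subgroup results would describe a different population from the routine referrals named in 3.2.1. The documents report neither how often values are missing nor how often responses are absent, so no size can be given for the number of patients affected or for any shift in the results.

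For the primary comparison, the finding is an exposure and not a demonstrated bias: exclusion comes after randomization, one route is discretionary, and identical handling in the two arms is not assured. The change is worth making because it decides who is analysed and costs little.

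**What to change.** 1. Reconcile 3.2.3, 3.2.4 and 3.3.3 into one objective threshold for missing values and one for artifacts, stated once and cross-referenced. Define critical measurement, and replace the examiner's discretion with that rule.
2. Apply the rule identically in both arms, without reference to allocation, and report exclusions by arm with reasons.
3. State that an absent response after a technically adequate attempt is a recorded result and is not missing. Limit *missing* to values not attempted or lost for technical reasons.
4. State in 5.2.5 whether studies excluded under this rule count towards the 5% missing-data limit.

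The cost is Protocol wording and one coding convention. The small downside is that the AI input and the data-completeness checklist must accept no-response entries.

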**3.3 Interventions**

**3.3.1 AI Algorithm Version**

The study will use INSPIRE version 1.0, a multi-agent framework built upon "ChatGPT-4o" LLMs hosted within the AZURE AI platform, using the AutoGen 0.4 library. The system utilizes a bidirectional sequential multi-agent architecture with SelectorGroupChat functionality, enabling dynamic, context-aware collaboration between AI agents.

**Technical Validation Metrics**

Prior to the trial, the model achieved the following performance metrics during retrospective analysis:

- accuracy of 92.2% for detecting normal versus abnormal tests
- Native Gemini 1.5-pro achived 62.6% accuracy for detecting normal versus abnormal tests
- INSPIRE demonstrated significantly higher AIGERS scores overall and across the domains of finding and clinical diagnosis, (p<0.001) in contrast to Gemini 1.5-pro.

**3.3.2 Input Data Acquisition and Selection**

The input data for the AI intervention will consist of:

1. Patient demographic information (age, sex, clinical indication)
2. Medical history relevant to neuromuscular outpatient clinic
3. Complete nerve conduction study data (tables of measurements)
4. Needle EMG recordings (quantitative and qualitative descriptions)
5. Visual representations of waveforms

**3.3.3 Handling Poor-Quality Input Data**

If the EDX data contains artifacts or is of insufficient quality, the following procedure will be implemented:

1. If specific measurements are missing but the overall study is interpretable, the report will be discarded base upon the examiner decision
2. If the data quality falls below a predetermined threshold (>30% of measurements affected by artifacts or >2 critical measurements missing), the case will be excluded from AI analysis and documented as a technical failure

For both arms, poor-quality data will be documented.

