**3.5 Participant Timeline**

The study will follow a simple timeline:

1. Screening and enrollment prior to scheduled EDX appointment
2. Randomization on the day of the EDX study
3. EDX testing performed according to standard clinical protocols
4. Report generation (either AI-assisted or physician-only)
5. Quality assessment and data collection
6. No follow-up visits required for the study (though patients may have clinical follow-up as determined by their treating physician)

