**4.1.3 Implementation**

The allocation sequence will be generated by a biostatistician not involved in patient enrollment. Research coordinators will enroll participants, and the treating neurologists will assign participants to interventions based on the randomization envelope.

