**4.2 Blinding**

Due to the nature of the intervention, the neurologists generating the reports cannot be blinded to the study arm. However, the three neurologists assessing the quality of the reports (outcome assessors) will be blinded to the method of report generation. Reports from both arms will be reformatted to a standard template to prevent identification of the study arm based on formatting or style.

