#### 5.2.5 Handling of Missing Data

Missing data will be addressed as follows:

1. Cases where EDX data quality is insufficient for AI analysis will be documented as technical failures
2. For the primary outcome analysis, we will use complete case analysis if missing data is <5%
3. If missing data exceeds 5%, multiple imputation techniques will be employed
4. Sensitivity analyses will be conducted to assess the impact of missing data on outcomes

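### Data-quality rules that act after randomisation allow reports to be discarded without a criterion and leave open whether failed cases stay in the primary comparison

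*Protocol*

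**What the plan says.** **Order of events.** Section 3.5 lists "Randomization on the day of the EDX study" as step 2 and the EDX test as step 3. Under Section 4.1.2 the envelope is "opened only after the participant has been enrolled and immediately before the EDX study begins". Section 4.1.3 says that "the treating neurologists will assign participants to interventions based on the randomization envelope", and Section 4.2 that "the neurologists generating the reports cannot be blinded to the study arm".

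**Poor data, Section 3.3.3.**
- Item 1: some measurements are missing but the study can be interpreted. Then "the report will be discarded base upon the examiner decision".
- Item 2: more than 30% of measurements have artefacts, or more than 2 critical measurements are missing. Then "the case will be excluded from AI analysis and documented as a technical failure".
- For the two arms jointly, the section asks only that poor quality be recorded.

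**Other places.** The data-level exclusions in Section 3.2.4 begin with "Incomplete measurement sets (missing amplitude, latency, or velocity data"; they name no arm. Section 5.2.5 states: "Cases where EDX data quality is insufficient for AI analysis will be documented as technical failures". Its next items give complete-case analysis below 5% missing, multiple imputation above 5%, and sensitivity analyses for missing data.

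**The concern.** Data quality cannot be judged until the test is done, and by then the arm is known to the treating neurologist. Any rule that removes a patient on data quality is therefore a post-randomisation exclusion. Such a rule is harmless only if it works the same way in both arms and does not depend on knowledge of the arm. Neither is assured here.

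Item 1 gives one person discretion over a report that could have been scored. Item 2 is worded for the AI side only. Poor recordings are plausibly the hardest to report and the lowest scoring. If more of them leave the AI arm than the control arm, the AI arm's mean AIGERS score rises without any benefit from AI.

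In item 2 cases the score need not be missing at all, because a neurologist can still write a report, as in the control arm. Section 6.3 itself counts technical failures of the system as AI performance errors, and Section 2.2 aims at added value in real clinical settings. Leaving such cases out of the comparison would sit badly with both.

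**Working it through.** **1. No figure of the plan to reproduce.** The protocol gives 200 patients, 100 per arm (Sections 3.6 and 5.2.1), without an effect size, SD, power or expected rate of poor recordings. The check is mainly one of reading; the arithmetic only shows scale.

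**2. The rules side by side.**

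| Place | Trigger | Consequence | Arm | Who decides |
|---|---|---|---|---|
| 3.2.4 | incomplete set of amplitude, latency or velocity data | excluded | not named | not stated |
| 3.3.3 item 1 | some measurements missing, still interpretable | report may be discarded | not limited | examiner, no criterion |
| 3.3.3 item 2 | >30% artefact or >2 critical missing | out of AI analysis | AI side only | numeric threshold |
| 5.2.5 item 1 | insufficient for AI analysis | documented | not stated | not stated |

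A study with one missing latency is excluded under 3.2.4, discretionary under item 1, and below the threshold of item 2. The consequences are also out of order: the milder defect can cost the whole report, the more severe one only the AI analysis.

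**3. Size if removal were from the AI arm only.** Assumptions, none from the protocol: a share f of AI-arm cases is dropped, these would have scored d SD below the rest, control loses nobody, and AI has no true effect.

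- Bias = f × d SD in favour of AI.
- Shift in z = f·d / √(1/100 + 1/(100(1 − f))).
- Type I error = P(|Z + shift| > 1.96), normal approximation, two-sided 5% as in Section 5.2.2.

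Example, f = 10%, d = 1: 0.10 / √(0.01 + 0.01111) = 0.10 / 0.1453 = 0.688, which gives 10.6%.

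| f | d (SD) | Bias (SD) | Type I error | Share of all 200 |
|---|---|---|---|---|
| 4% | 0.5 | 0.02 | 5.2% | 2% |
| 4% | 1 | 0.04 | 5.9% | 2% |
| 8% | 1 | 0.08 | 8.6% | 4% |
| 10% | 0.5 | 0.05 | 6.4% | 5% |
| 10% | 1 | 0.10 | 10.6% | 5% |

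**4. Check with the rank test.** A simulation used the two-sided Mann-Whitney test (for two groups equivalent to the planned Kruskal-Wallis test), 4,000 runs per setting. Scores were centred at 0.75 and clipped to 0–1, with SD 0.15 or 0.20 and poor recordings scoring 0.1 to 0.3 lower (all assumed). Removal from the AI arm only gave type I error of 4.4–6.6% at 4% dropped and 6.2–16.1% at 10%. The upper ends exceed the table because a drop of 0.3 is 1.5 to 2 SD.

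**5. After the fix.** With 20% poor recordings scoring 0.3 lower, analysing all 200 gave about 4.6%. Removing the same kind of case from both arms, regardless of allocation, gave 4.8–4.9%. The mean difference was about 0 in both.

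**6. The missing-data rule.** If dropped cases count as missing and the percentage is taken over all 200, then 10 dropped from one arm is exactly 5%, which Section 5.2.5 assigns neither to complete cases nor to imputation. Above that, imputation would apply and the formula in step 3 no longer describes the planned analysis.

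**The case against.** Several stronger readings are tempting, and the documents do not support them.

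- **An unblinded examiner drops patients from the AI arm only.** No rule does both. Item 1 is discretionary but open to either arm; item 2 concerns the AI side but follows a threshold. That the examiner knows the arm is a likely inference from Sections 4.1.2, 4.1.3 and 4.2. The term is undefined, and Section 3.3.4 allows a technician to perform the study.
- **Item 2 cases leave the primary comparison.** The words could mean only that INSPIRE does not process the case, or that it is left out of the AI-alone comparison in Section 5.2.2, while the physician's report stays in its arm. The protocol does not say.
- **Control patients with poor data are always kept.** Sections 3.2.3 and 3.2.4 name no arm. Applied trial-wide, they would remove poor recordings from both arms, and the one-sided bias would largely vanish.
- **Section 5.2.5 classes these cases as missing.** The section heading suggests it, but the text says only that they are documented. Sensitivity analyses are planned, and imputation could condition on recorded data quality.
- **The type I error is very large.** The formula gives 26.6% at f = 20% and d = 1, but that is 10% of the trial. If those cases count as missing, imputation would be triggered instead.

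Definitions of analysis sets are commonly left to the SAP, so their absence alone is no fault. What stands is what the protocol does state: a discard without a criterion after allocation, an AI-side rule with no counterpart and no stated destination for the patient, and two thresholds that disagree. The ambiguity does not protect the trial, since the reading could be chosen once scores are known.

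**Conclusion.** The point holds as a defect in the stated rules, not as a demonstrated bias. Sections 3.3.3, 3.2.4 and 5.2.5 together allow selective removal of hard cases after randomisation, and no statement in the protocol restores the randomised groups. The discretionary discard is the clearest fault, because it holds under every reading of the other rules.

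The size is uncertain. It depends on an assumed share of dropped cases, an assumed deficit in their scores, and removal from the AI arm only. Under those assumptions the distortion is slight when about 4% of the arm is dropped and appreciable at 10%; if exclusion is symmetric and independent of allocation, it is about nil.

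**What to change.** 1. In Section 3.3.3, delete the discard at the examiner's discretion.
2. In Sections 3.3.3 and 5.2.5, state that every randomised patient with a completed EDX study is analysed in the assigned arm. Where INSPIRE cannot run or the data fail the threshold, the neurologist's own report is scored as that patient's report. Such a score is then observed, so there is nothing to impute.
3. Reconcile Sections 3.2.4 and 3.3.3 into one definition of poor data quality, and use it to flag cases in both arms, not to remove them.
4. Make the analysis that leaves out flagged cases from both arms a sensitivity analysis, and report the number flagged by arm.

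An assessor unaware of allocation is not needed for the primary analysis, because the flag no longer decides who is in it.

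**Cost.** A change of wording and no extra patients. The estimated AI effect may be slightly smaller, because failures of the tool count in its arm.
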